### Blinding

The lead student investigator will not be blinded to participant allocation, and so any follow up visits and testing will be conducted by a blinded research assistant. The therapist who will follow patients randomized to Group 2 will not be blinded as they will only have access to patients in Group 2.

### Intervention

PREPS is a 6-week multimodal program that consists of a) a website with video modules, containing both exercises and education on the shoulder replacement journey, as well as b) an education booklet replicating the online information. This multimodal format allows for increased accessibility of information for an older adult population. The program will be completed within a participant’s home, and on their own time over the course of 6 weeks. Patients will be able to replay videos as many times as needed. Interactive quizzes will be displayed throughout the program to capture learning.

#### Exercise content in PREPS

Participants will have the opportunity to complete a short exercise program consisting of five exercises (Hand behind back, forward flexion, ball to the wall, shoulder blade squeezes and pendulums) that are appropriate for pre-surgical rehabilitation. Participants will learn these exercises on screen and then can follow along to complete them. Each exercise video is 2 minutes long. Participants should complete 10 reps, 3 sets of each exercise in the video. This would require approximately 15 minutes from start to finish if a patient completes all five videos. Participants will record their progress on a program sheet, indicating the number of sets and repetitions completed, and any modifications they made during the session.

#### Education content in PREPS

Participants will be guided through an education program that will cover a variety of 7-8 topics regarding before and after surgery preparation. Individuals will have flexibility as to when and how often they review material. The participants will be directed to complete on-screen interactive quizzes to re-enforce learning. Participants are encouraged to pose any questions regarding the material within the education modules to the research team for further clarification. Research assistants will keep a log of calls and questions to inform potential additions or changes to the existing material. Participants will be expected to complete a log to reflect how much of the program they completed and how often each module was reviewed. This will be accessed in their workbooks.

#### Therapist involvement

For participants in Group 2, at the end of weeks 1 and 5, a physical therapist will contact the patient by phone to review the exercise performance. They will implement a teach-back type approach to assess adherence/ health literacy, and address questions or concerns patients have with the education or exercise material. The therapist may suggest adjustments to the exercise program or additional resources to address individual needs/concerns. Phone calls should take approximately 15-30 mins each. To inform treatment fidelity, the therapist will complete a checklist following each call.

#### Time

The intervention groups will be asked to participate in the pre-operative program (6 weeks) before surgery. After surgery, they will not be required to continue with the PREPS program. Standard practice post-operative rehabilitation will be continued with all participants. Patients have the choice on where they want to receive post-surgery rehabilitation but, we will ask participants to track their activity and adherence to physical therapy through a log for 6-month post-operatively.

#### Comparator

The control group will not receive the new preoperative program. They will participate in the standard of care at the HULC, which consists of regular appointments with their surgeon, check-ins with the pre-admit staff at HULC, and the webinar class with a physiotherapist and occupational thereapist. This webinar class, is a one time class with both anatomical and reverse shoulder replacement patients: caregivers are also welcomed. The class consists of two parts, part one focuses on the anatomy of the shoulder, some aspects of the surgurical procedure and anaesthesia information led by a physiotherapist. Part two focuses on how to prepare your environment for after surgery such as clothing, bathing and sleeping, lead by an occupational therapist. The class is an hour long, on an online synchronous platform, and runs monthly. Patients are requested to attend the class once prior to surgery.

#### Data collection

A study manual describing the operating procedures, consent forms, and data forms are in the PREPS Study Manual, accessible at HULC. All data collection assessments will be collected on paper and entered into a de-identified database on a secure and encrypted hospital computer. This information will only be accessible to authorized study personnel.

### Outcomes

All participants, regardless of group will complete all study visits (consisting of 2 pre-operative visits [baseline and one day before surgery] and post-operative visits at 6 weeks, 3 months, 6 months and 1 year). At baseline, we will collected demographic characteristics such as: sex, height, weight, reason for surgery, symptom duration, affected shoulder, and dominant hand. In the pilot study, we will test all outcomes to determine which measures will be moved forward to the full study.

#### Feasbility outcomes

• Recruitment Rate: We will proceed with the larger trial if we are able to recruit 90 participants within 24 months, and if at least 50% of eligible participants consent to participate.• Adherence: Adherence to the education program will be considered adequate if 80% of all participants in the intervention groups complete the full online program and report it on the log. Exercise programs will be considered adequate if 60% of participants in the intervention groups report exercise at least 3 times per week.• Content Acceptability: Content acceptability will be assessed using item 7 on the Surgurical Satisfaction Questionnaire, where acceptability will be considered adequate if 60% of participants were satistifed with the treatment (score of atleast 4/5 on item 7).• Study Acceptability: Study acceptability will be assessed using item 10 on the Surgurical Satisfaction Questionnaire, where acceptability will be considered adequate if 60% of participants were satistifed with the study (score of atleast 4/5 on item 10).• Treatment Fidelity: If 80% of the content was covered in 80% of phone calls fidelity checklist assessment, fidelity will be considered acceptable.

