### Participants

We will recruit volunteers over the age of 18 years, who have been consented for a shoulder replacement surgery at the HULC, to fulfill a sample size of 90 participants, with 30 in each arm. The sample size is based on current recommendations for pilot studies, objectives of this study, and feasibility of being able to complete recruitement of the full powered trial in 2 years. Since our sample size is 168 in the full powered trial, we aim to collect half of this in 1 year. See below for full trial sample calculation.

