#### Outcomes to be included within the full study

The following outcomes listed below will be included in the pilot study since participants in the pilot may be rolled into the full study (see Table 1). The primary outcome in the full study will be the SPADI and secondary outcomes will include:• *General health status* as measured by EQ-5D global health^
13
^ and Single Assessment Numeric Evaluation^
14
^• *Shoulder specific function tests*: American Shoulder and Elbow Surgeon’s Score,^
15
^ Shoulder Pain and Disability Index,^
16
^ Simple Shoulder Test^
17
^• *Patient satisfaction*: Surgical Satisfaction Questionnaire (SSQ-8)• *Patient Anxiety *as measured by the Decisional Regret Scale,^
18
^ and Patient Anxiety Symptom Scale (PASS)• *Adherence to rehabilitation* as recorded in the patient log (see Table 1)• *Performance measures*: goniometric measures of shoulder range of motion

**Table 1. table1-17589983251345393:** DRS, decisional regret scale; SPADI, shoulder pain and disability index; SANE, Single assessment of the numeric evaluation; PPQ, patient participation questionnaire; SSQ-8, surgical satisfaction questionnaire; SAQ, surgical anxiety questionnaire.

Variable/outcome	Hypothesis	Outcome measure	Method of analysis
Recruitment	15-16/ month And 50% eligible to participate	Research log	Percentages reported

Adherence	80% of all participants in the intervention groups complete the PREPS program, and 60% report exercise at least 3 times per week	Patient log	Percentages reported
Content acceptability	60% of participants found the treatment useful and helpful on item 7	Surguical satisfaction quesionnaire	Means and standard deviation reported
Study acceptability	60% of participants found the treatment delivery acceptable, and reported being likely to use this treatment again and recommend it to others, on item 10	Surguical satisfaction quesionnaire	Means and standard deviation reported
Treatment fidelity	If 80% of phone calls and recorded notes were documented on the checklist by the therapist	Therapist checklist	Means and standard deviation reported

The majority of assessments will occur at baseline, day before surgery, and post-surgery at 6 weeks, 3 months, 6 months and 12 months. With the exception of some measures, as detailed in Figure 1, of the schedule throughout the research study.

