## Plan for statistical analyses

Descriptive quantitative variables will be presented as means and standard deviations and the categorical variables will be presented as percentages. Following pilot study guidelines, criteria to progress from feasibility to definitive trial are listed in Table 2 below. Each primary feasibility outcome measure will be assessed separately, and overall progression will be determined by the worst-performing criterion. If all signals fall into the green zone, we will proceed to the trial without changes. If none of the signals fall into the red zone but at least one falls into the amber zone, the design of the trial procedures will be amended before proceeding to the definitive trial. If at least one signal falls into the red zone, we will not proceed to the definitive trial without making significant improvements to protocol and re-assessing feasibility.

**Table 2. table2-17589983251345393:** Progression criteria for feasibility.

	Proceed	Proceed with protocol amendment	Significant protocol amendment
Recruitment *N* = 90 in 12 months	15-16/ month and 50% eligible to participate	13-14/ month and 40% eligible to participate	<12 /month and 30% eligible to participate
Adherence	• 80% of all participants in the intervention groups complete the online program, and 60% report exercise at least 3 times per week	• 60% of all participants in the intervention groups complete the online program, and 40% report exercise at least 3 times per week	• 25% of all participants in the intervention groups complete the online program, and 25% report exercise at least 3 times per week
Content acceptability	• 60% of participants found the treatment useful and helpful with a score of 7/10	• 40% of participants found the treatment useful and helpful with a score of 7/10	• <40% of participants found the treatment useful and helpful with a score of 7/10
Study acceptability	• 60% of participants found the treatment delivery acceptable, and reported being likely to use this treatment again and recommend it to others with a VAS score of 7/10	• 40% of participants found the treatment delivery acceptable, and reported being likely to use this treatment again and recommend it to others with a VAS score of 7/10	• <40% of participants found the treatment delivery acceptable, and reported being likely to use this treatment again and recommend it to others with a VAS score of 7/10

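### The recruitment progression rule has two windows (24 and 12 months) and a monthly target with no stated unit, so one pilot result can pass in the text and miss green and amber on pace in Table 2.

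*Protocol article*

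**What the plan says.** Recruitment pace appears in four places in the protocol article.

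- **Feasibility outcomes, Recruitment Rate:** "We will proceed with the larger trial if we are able to recruit 90 participants within 24 months", with the added condition "if at least 50% of eligible participants consent to participate".
- **Table 1, Recruitment row:** "15-16/ month And 50% eligible to participate".
- **Plan for statistical analyses, Table 2, Recruitment row:** the row label gives "90 in 12 months". The cell for proceeding (green) is "15-16/ month and 50% eligible to participate". The middle cell (amber) has 13-14 per month with 40%. The last cell (red) is "<12 /month and 30% eligible to participate".
- **Participants:** the pilot is "to fulfill a sample size of 90 participants, with 30 in each arm", and the reasoning is "Since our sample size is 168 in the full powered trial, we aim to collect half of this in 1 year". The same section aims to recruit the full trial in 2 years.

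The text above Table 2 has each primary feasibility outcome assessed on its own and lets the poorest one settle overall progression. One red result means no definitive trial until the protocol has been substantially improved and feasibility tested again.

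**The concern.** Recruitment is one of the primary feasibility outcomes named in the Introduction, and it feeds a rule in which a single poor result decides. Such a rule protects against judging success after the fact only if the same data always give the same answer. Here the window differs by a factor of two between the text and Table 2. Within the Table 2 row, the label implies half the monthly figure in the green cell unless that figure counts something other than enrolled patients. Someone holding the final recruitment count could cite the text and proceed, or cite Table 2 and stop or amend.

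**Working it through.** **Inputs.** Pilot size is 90. The windows are 24 months (Feasibility outcomes) and 12 months (Table 2 row label). Monthly cuts are 15-16, 13-14 and below 12, with shares of 50%, 40% and 30% (Table 2). Full-trial size is 168, half of it in 1 year (Participants). I take the percentage in the tables to be the consent share among eligible patients, as the Feasibility outcomes text words it.

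**The plan's own figures.** The 168 reproduces from Sample size estimation: 2 × (1.64 + 0.84)² × 21.3² × (1 − 0.81²) / (10.3 − 4.26)² = 52.6, so 53 per group. With 5% added this is 56, and 3 × 56 = 168. The green pace does not follow directly from its row label: 90 / 12 = 7.5 per month, not 15-16.

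**Enrolment pace implied by each statement (patients / months).**

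- 90 within 24 months: 90 / 24 = 3.75 per month, as a minimum
- 90 in 12 months: 90 / 12 = 7.5 per month
- Half of 168 in 1 year: 84 / 12 = 7.0 per month

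**Reading A: the monthly figure counts patients enrolled.** Green gives 90 / 15 = 6.0 to 90 / 16 = 5.6 months, or 15 × 12 = 180 to 16 × 12 = 192 patients in 12 months. The paces 7.5, 7.0 and 3.75 are all below the red limit of 12. At 12 per month, 90 patients take 90 / 12 = 7.5 months, so any pilot taking longer than that is below the red limit on pace.

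**Reading B: the monthly figure counts eligible patients approached.** Enrolled in 12 months = approached per month × consent share × 12.

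- Green: 15 × 0.5 × 12 = 90 to 16 × 0.5 × 12 = 96. This agrees with the row label.
- Amber: 13 × 0.4 × 12 = 62.4 to 14 × 0.4 × 12 = 67.2.
- Red limit: 12 × 0.3 × 12 = 43.2.

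Converting the other statements to approaches at 50% consent:

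- Participants section: 7.0 / 0.5 = 14 per month, which is amber on pace.
- A pilot that just meets the text: 3.75 / 0.5 = 7.5 per month, below 12. The text requires at least 50% consent, so 7.5 is the most such a pilot would approach; higher consent lowers it.

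At 50% consent, 12 approached per month is 6 enrolled, and 90 / 6 = 15 months. A pilot that takes more than 15 and up to 24 months therefore passes the text and is below 12 in Table 2.

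**Mixed and in-between results.** A pilot enrolling 7.5 per month with 50% consent, under reading A, is below 12 on pace but meets the green consent share. The red cell asks for low pace and 30% together, so it fits no cell. Exactly 12 per month, averages between 12 and 13 or between 14 and 15, and consent shares between the listed values are also unplaced.

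**The case against.** The strongest defence is reading B. The green cell pairs the monthly figure with a 50% share, and 15 × 0.5 × 12 = 90 is exactly the row label. On that reading Tables 1 and 2 are consistent with 90 in 12 months, and the Participants figure (84 in a year) is close. The 24-month window is also an upper limit rather than a planned pace, so a pilot that enrols 90 in 12 months satisfies it too. These arguments stand, and they rule out some stronger claims.

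A reader might infer that a pilot recruiting exactly to plan is graded red. The documents do not support that as a flat statement. It needs reading A, which neither table states, just as neither states reading B. Even on reading A, the red cell joins pace with 30% consent, so 7.5 per month at 50% consent is unclassified rather than clearly red. The rule that the poorest result decides is stated across feasibility outcomes, not for the two halves of one cell.

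The defence does not remove the 24-month window. A pilot that only just meets the text is below 12 per month whichever unit is used. Nor does it supply the missing unit label.

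**Conclusion.** The recruitment criterion contradicts itself and needs correcting. Two parts need no interpretation: the window is 24 months in one place and 12 in another, and the monthly target has no stated unit. On either reading of the unit, some pilots pass the text and fail both green and amber on pace in Table 2. These are pilots taking more than 7.5 months if the figure counts enrolled patients, or more than 15 months if it counts approached patients at 50% consent, in each case up to 24 months.

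How far the tables disagree with the rest of the plan depends on the unit. If enrolled, the green pace is 15 / 7.5 = 2.0 to 16 / 7.5 = 2.1 times the row label, and the Participants pace of 7 per month is below the red limit. If approached, the green cell and row label agree and the Participants pace is amber. The conversions assume that the tables' percentage is the consent share. The effect is on the progression decision; no treatment-effect estimate is involved.

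**What to change.** 1. State one recruitment window, the same in the Recruitment Rate bullet and in Table 2. The documents do not show which of 12 or 24 months is intended, so the sponsor must choose.
2. Label the monthly figure in Tables 1 and 2 as patients enrolled or eligible patients approached.
3. Derive contiguous green, amber and red cuts from that window and unit. With enrolled patients and 12 months, green is 7.5 per month. With approached patients, 15-16 can stay, and the enrolled count should be graded consistently with the 50%, 40% and 30% shares. Halving the present amber figure would not do this: 13 / 2 = 6.5 enrolled per month, whereas Table 2's own 40% gives 13 × 0.4 = 5.2.
4. Grade pace and consent share separately and let the worse one decide, so that mixed results have a class.

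The sponsor sets the amber and red cuts, before recruitment data are reviewed. The cost is a wording amendment to one bullet and two table rows. Because the study already has ethics approval, the change may need to be filed as an amendment. It needs no extra patients or procedures.

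### The two acceptability progression criteria give no single determinable result: instrument, scale and cut-off differ between the outcomes section and Table 2, and the denominator is left open

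*Protocol article*

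**What the plan says.** The criteria appear in three places in the protocol article.

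- **Feasibility outcomes section.** Content: "acceptability will be considered adequate if 60% of participants were satistifed with the treatment (score of atleast 4/5 on item 7". For the other criterion, "Study acceptability will be assessed using item 10 on the Surgurical Satisfaction Questionnaire", and "acceptability will be considered adequate if 60% of participants were satistifed with the study (score of atleast 4/5 on item 10".
- **Table 1.** Content: "60% of participants found the treatment useful and helpful on item 7", with no cut-off. Study acceptability keeps item 10 but describes acceptable delivery, willingness to use the treatment again and willingness to recommend it. The analysis entry for both rows is "Means and standard deviation reported".
- **Table 2 (progression criteria).** Green for content: "60% of participants found the treatment useful and helpful with a score of 7/10". Study acceptability asks that participants would, among other things, "recommend it to others with a VAS score of 7/10". Green is 60%, amber 40% and red below 40%.

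The list of outcomes for the full study names the instrument as "Surgical Satisfaction Questionnaire (SSQ-8". The adherence criterion is limited to the intervention groups in all three places; neither acceptability criterion carries that limit in any of them. All groups attend all visits (Outcomes), and the control group does not receive the new programme (Comparator). The statistical analysis section grades each feasibility outcome separately and lets the worst one decide progression.

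**The concern.** Acceptability of PREPS is the first research question and supplies two of the five rows in Table 2. Because the worst row decides, either acceptability row alone can turn a straightforward go into an amended protocol or a return to feasibility testing. A threshold with that role should yield one answer from one data set. Here the section that defines the measures and the table that makes the decision give different scales and cut-offs, and for study acceptability a different construct as well. The set of patients to be counted is not fixed either. The grade could therefore depend on which version is applied once the data are in, which is what prespecified progression criteria are meant to prevent.

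**Working it through.** The plan gives no calculated figure for acceptability, so there is none to reproduce. The inputs are 90 participants, 30 per arm (Participants), hence 60 in the PREPS arms and 30 in standard care, and the 60% and 40% limits of Table 2.

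**1. The definitions side by side**

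| | Feasibility outcomes | Table 1 | Table 2 |
|---|---|---|---|
| Content: measure | item 7 | item 7 | no item named |
| Content: cut-off | at least 4/5 | none | 7/10 |
| Study: measure | item 10 | item 10 | VAS |
| Study: cut-off | at least 4/5 | none | 7/10 |
| Study: construct | satisfaction with the study | delivery, reuse, recommending | delivery, reuse, recommending |
| Denominator (both) | participants | participants | participants |

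**2. Are 4/5 and 7/10 the same point?** The documents do not give the range of the item, so assume linear rescaling to 0–10. On a 1–5 scale, 4 maps to (4 − 1)/(5 − 1) × 10 = 7.5. On a 0–5 scale it maps to 4/5 × 10 = 8. Conversely, 7/10 maps to 1 + 0.7 × 4 = 3.8 on a 1–5 scale. If 7/10 were only a restatement of a whole-number 1–5 item, a cut at 3.8 would pick out the same patients as a cut at 4. A VAS is a separate measurement, however: a mark between 7 and 7.5 passes Table 2 yet lies below the rescaled 4/5. How many patients this would affect cannot be worked out from the documents.

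**3. Denominator.**
- PREPS arms only: 0.60 × 60 = 36 satisfied for green.
- All 90: 0.60 × 90 = 54 satisfied for green.
- PREPS users needed when all 90 count = 54 − 30 × (satisfied share among controls). The control shares are assumed:

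| Controls satisfied | PREPS users needed |
|---|---|
| 50% | 39/60 (65%) |
| 60% | 36/60 (60%) |
| 70% | 33/60 (55%) |
| 80% | 30/60 (50%) |
| 90% | 27/60 (45%) |
| 100% | 24/60 (40%) |

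The error can run the other way. With 36 of 60 PREPS users and 40% of controls (12 of 30) satisfied, the total is 48/90 = 53%, which is amber although the PREPS arms alone are green.

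The chance of green is P(X + Y ≥ 54) with all 90, where X ~ Bin(60, p) for PREPS and Y ~ Bin(30, q) for controls, and P(X ≥ 36) with the PREPS arms only:
- p = 0.50, q = 0.80: 0.55 with all 90, 0.08 with PREPS only.
- p = 0.70, q = 0.40: 0.55 with all 90, 0.96 with PREPS only.

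**4. Mean against percentage (60 patients, cut at 4).**
- 30 scores of 5 and 30 of 3: mean (150 + 90)/60 = 4.0; share at 4 or more 30/60 = 50%, not green.
- 36 scores of 4 and 24 of 1: mean (144 + 24)/60 = 2.8; share 36/60 = 60%, green.

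A mean and SD alone do not settle the criterion.

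**The case against.** Three stronger readings are tempting, and the documents support none of them in full.

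**That the plan counts standard-care patients.** No sentence says so. The first research question is about PREPS, and Tables 1 and 2 speak of the treatment, so a reader could take PREPS recipients to be meant. Attending every visit does not prove that every item goes to every arm: some measures are said to follow a different schedule, and the schedule figure is not shown here. For satisfaction with the study, as the Feasibility outcomes section words it, including controls would be legitimate. What stands is that the limit written out for adherence is absent for acceptability, so the literal reading includes controls and the text does not exclude it. The 24-of-60 figure is also an extreme case: all controls satisfied, all 90 counted, nobody missing.

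**That the criteria cannot show whether PREPS is acceptable.** The mean and SD entry does not prevent the percentage from being computed, because item scores are collected. The statistical analysis section says that categorical variables are given as percentages, and the fidelity row, also a percentage criterion, carries the same entry. This looks like a labelling slip, and nothing says that the mean will decide.

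**That item 10 does not exist.** That the questionnaire labelled SSQ-8 has eight items is an assumption from its label. The form is not shown, and the Feasibility outcomes section does not use the label. It is a fair query, not a demonstrated error.

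None of this touches the conflict of scale and cut-off, which nothing in the article resolves.

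**Conclusion.** The point holds in this form: as written, the two acceptability criteria have no single determinable result.

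- **Firm, on the text alone:** the 4/5 against 7/10 conflict, the VAS named only in Table 2, and the shift in what study acceptability means. They matter because Table 2 drives the decision and its worst row governs. The documents give no basis for saying how often the two rules would disagree.
- **Firm but minor:** a reporting entry in Table 1 that does not match a percentage criterion.
- **Ambiguity, not a stated rule:** the denominator. If it is read literally, the green requirement moves from 36 of 60 to 54 of 90, and control satisfaction can shift the result in either direction. The sizes rest on assumed control satisfaction and complete data.
- **Query only:** item 10 on a questionnaire labelled SSQ-8.

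**What to change.** 1. For each criterion, state one instrument, item, scale (with its range) and cut-off, in identical terms in the Feasibility outcomes section, Table 1 and Table 2. If the VAS is intended, add it to the outcome list; if not, remove it and the 7/10 figures.
2. Say whether study acceptability means satisfaction with study procedures or with the PREPS treatment, and use that meaning throughout.
3. Name the denominator. Limit content acceptability, and any item about the PREPS treatment, to the two PREPS arms (green at 36 of 60 if all respond). Satisfaction with study procedures may include all three arms.
4. In Table 1, report the percentage meeting the cut-off with a 95% CI, in place of or alongside the mean and SD.
5. Check that the cited item 10 exists on the form in use, and correct the label or the item number if it does not.

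The cost is a wording change in three places and, at most, one or two questions added to an existing form. It should be settled before anyone looks at the acceptability data.
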